## Discussion

6

This study outlines a rigorously designed pilot trial aimed at comparing the effects of multi-angle ISO-RT and DYN-RT on muscle performance, body composition, and recovery-related responses. While DYN-RT has traditionally been the gold standard for improving muscular strength and hypertrophy, multi-angle ISO-RT offers a promising alternative by potentially overcoming the joint-angle specificity of conventional isometric protocols. Nonetheless, high-quality controlled trials are needed to determine whether these theoretical advantages translate into superior or comparable adaptations in practice. This trial is among the first to directly compare these two training modalities using a comprehensive battery of outcome measures. In addition to primary outcomes, the study evaluates secondary physiological markers such as muscle hypertrophy, power, endurance, and muscle oxygenation. In the current study, muscle oxygenation of the vastus lateralis will be assessed before and after dynamic and isometric muscular endurance tests using mNIRS technique, which is a non-invasive, real-time technique for monitoring local tissue oxygenation and blood volume dynamics. NIRS enables continuous quantification of changes in oxygenated and deoxygenated hemoglobin, offering valuable insights into the muscle's metabolic and vascular responses to exercise. By evaluating these parameters during both endurance protocols and standardising the signal through post-test maximal isometric contractions, this method allows for direct comparison of the physiological demands imposed by ISO-RT and DYN-RT. These data may help clarify how different resistance training modalities influence local muscle oxygenation and recovery capacity.

The inclusion of subjective recovery metrics, including perceived muscle soreness and sleep quality, provides a more holistic view of training responsiveness, offering insights into how these modalities may differentially impact recovery, tolerability, and long-term adherence. Together, these data will yield preliminary effect estimates and feasibility indicators to inform the design and implementation of larger-scale, adequately powered studies. In doing so, the findings will contribute to the growing evidence base needed to develop individualised and context-specific RT guidelines.

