**Methods:**

In this pilot randomised controlled trial, 20 healthy adults (≥18 years) will be randomly assigned to either the ISO-RT or DYN-RT group (n ​= ​10 per group). Both groups will complete a full-body resistance training program twice weekly for six weeks. The key distinction lies in the execution of the chest press and leg press exercises—performed isometrically in the ISO-RT group and dynamically in the DYN-RT group. All outcomes will be assessed at baseline and post-intervention.

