Beyond muscle strength and hypertrophy, ISO-RT and DYN-RT may elicit distinct physiological and perceptual responses that influence training feasibility, recovery, and long-term adherence. For example, differences in local metabolic stress and fatigue accumulation could affect post-exercise recovery [11], yet these factors remain underexplored. Muscle oxygenation, which reflects real-time oxygen delivery and utilisation, is one such understudied variable. Although near-infrared spectroscopy (NIRS) offers a non-invasive means of assessing this, direct comparisons between ISO-RT and DYN-RT using NIRS are currently limited. Equally important are markers of recovery, such as muscle soreness and sleep quality, which can affect training tolerance and compliance over time. Despite their relevance, the influence of muscle soreness and sleep quality on adaptations and adherence across RT modalities remains poorly defined. Together, these gaps underscore the need for research that moves beyond traditional outcome measures to capture a more comprehensive understanding of responses to ISO-RT and DYN-RT.

To address these gaps, the current pilot study investigates the feasibility and preliminary efficacy of a novel multi-angle ISO-RT protocol in comparison to DYN-RT. A comprehensive set of outcomes will be evaluated, including muscular strength, hypertrophy, isometric and dynamic muscle endurance, fatigue recovery, muscle oxygenation, muscle soreness, and sleep quality. The findings will offer foundational insights to guide the design of future large-scale trials and support evidence-based integration of ISO-RT into both athletic and clinical RT settings.

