### Pre-testing familiarization session

3.6

To minimise learning effects that could otherwise inflate post-intervention performance outcomes, all participants will complete a dedicated familiarisation session prior to baseline testing. This session is particularly important given that participants are inexperienced with structured RT and the pneumatic resistance equipment used in this study. The session will include guided, hands-on instruction covering all outcome measures (i.e., 1RM dynamic strength, MVC, muscle power, and muscular endurance). Participants will be instructed on proper lifting techniques, breathing control, equipment handling, and movement cadence specific to each test (e.g., 2-1-2 tempo for dynamic lifts, 5-s holds for isometric efforts). They will also be introduced to equipment feedback systems, including real-time force and power displays, to ensure familiarity with test procedures. The goal of this session is to ensure that participants are confident, consistent, and technically proficient during all baseline assessments. This approach enhances the accuracy, reliability, and reproducibility of performance data across timepoints.

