### Dynamic muscular endurance

4.4

Dynamic muscular endurance for the chest press and leg press will be evaluated using Keiser pneumatic resistance equipment, set at a standardised load of 60 ​% 1RM. Participants will perform as many repetitions as possible with proper form, adhering to the 2-1-2 ​s cadence (2-s concentric, 1-s pause, 2-s eccentric) used during training sessions. The test will be terminated when the participant is unable to complete a repetition with proper form or maintain the prescribed cadence for two consecutive repetitions. Recorded metrics will include the total number of repetitions, total work performed, as well as the velocity and power generated during the first and last repetitions.

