### Isometric muscular endurance

4.5

Isometric muscular endurance for the chest and leg press will be assessed using Keiser pneumatic RT equipment. Participants will perform intermittent isometric contractions set at 80 ​% of their predetermined MVC. Equipment adjustments will ensure participants’ joints are positioned at the midpoint of the concentric phase. The protocol comprises repeated cycles of a 5-s isometric contraction at 80 ​% MVC followed by a 5-s rest interval. The ISOTrainer live visual feedback module will enable participants to maintain accurate and consistent contraction intensity throughout the test. The test will terminate when participant-generated force falls below 50 ​% MVC during two consecutive repetitions. Recorded metrics will include the total number of successful contractions (repetitions) and the total time to exhaustion (in seconds).

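### NIRS at the two endurance tests can show how training changes the oxygenation response to each test, not the direct comparison of ISO-RT and DYN-RT demands that the Discussion claims

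*Protocol article*

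**What the plan says.** The Introduction (section 1) lists muscle oxygenation among the understudied responses, says that "direct comparisons between ISO-RT and DYN-RT using NIRS are currently limited", and offers the trial as a way to address such gaps. Oxygenation is a secondary outcome in the Abstract and in sections 5.2 and 6.1.

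Section 4 has no subsection on NIRS. The procedure appears only in section 6 (Discussion), where "muscle oxygenation of the vastus lateralis will be assessed before and after dynamic and isometric muscular endurance tests". Two sentences later the timing is put differently: "By evaluating these parameters during both endurance protocols and standardising the signal through post-test maximal isometric contractions". That same sentence ends with the claim at issue, that "this method allows for direct comparison of the physiological demands imposed by ISO-RT and DYN-RT". The sentence after it is more cautious: it says the data may help to show how training modalities affect local oxygenation and recovery capacity.

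The two tests are defined in sections 4.4 and 4.5. In the dynamic test, "Participants will perform as many repetitions as possible with proper form" at 60% 1RM on the 2-1-2 cadence. In the isometric test, "The protocol comprises repeated cycles of a 5-s isometric contraction" at 80% MVC, each followed by 5 s of rest, at one mid-range position. Section 5.2 analyses oxygenation with a two-way repeated measures ANOVA, with time (pre, post) within subjects and group (ISO-RT, DYN-RT) between subjects.

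**The concern.** In this article ISO-RT and DYN-RT name the two randomised training programmes (Abstract, sections 3.1 and 3.2). A statement about the demands they impose is therefore about what happens in the muscle while a person trains in one mode or the other. The recordings on which the sentence relies are taken at tests, not in training bouts, and the planned model asks how the response to those tests changes over six weeks. The stated conclusion and the planned estimate answer different questions.

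Section 6 is the only place where the article says what NIRS is for, so this sentence serves as the stated interpretation of a named secondary outcome. If it stands, a group difference in change could be reported as a difference in training demand. That reading could then carry into the larger trial that the pilot is meant to inform (section 5.1).

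**Working it through.** The point concerns what is measured, when and in whom. No sample size, power or alpha figure enters, and the plan gives no figure to reproduce. The check sets the sections side by side and asks what each available contrast would estimate.

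**Contrast 1: arm against arm, within one test (the section 5.2 model)**

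- Time points: the Abstract states that "All outcomes will be assessed at baseline and post-intervention".
- Who is tested: section 3.6 says that "all participants will complete a dedicated familiarisation session prior to baseline testing", covering the performance tests including muscular endurance, with no split by arm. Together with the time-by-group model, this implies that both arms take both tests.
- At baseline neither arm has begun its programme, so a group difference there says nothing about either training mode.
- The informative term is the group-by-time interaction: (post − pre in ISO-RT) − (post − pre in DYN-RT), for the same test. It estimates the difference between programmes in how the oxygenation response to that test has changed, which is adaptation.

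**Contrast 2: dynamic test against isometric test**

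The section 5.2 model has no factor for test type, so this contrast is not planned. If it were made, contraction mode would not be the only difference:

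| Feature | Dynamic test (4.4) | Isometric test (4.5) |
|---|---|---|
| Load | 60% of 1RM | 80% of MVC |
| Cycle | 2 + 1 + 2 = 5 s, no rest between repetitions described | 5 s on + 5 s off = 10 s |
| Position | moving repetitions | one fixed midpoint |
| Stop rule | form or cadence lost | force below 50% MVC in two consecutive repetitions |

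Duty cycle = contraction time / cycle time.

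- Dynamic: 5/5 = 100%, counting the 1-s pause as loaded. If the pause is counted as unloaded, 4/5 = 80%.
- Isometric: 5/(5 + 5) = 50%.

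Time-averaged nominal load = duty cycle × relative load.

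- Dynamic: 1.00 × 0.60 = 0.60 of 1RM (0.80 × 0.60 = 0.48 if the pause is unloaded).
- Isometric: 0.50 × 0.80 = 0.40 of MVC.

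These values sit on different reference scales (1RM and MVC) and cannot be subtracted. They show only that the tests were not built to be matched. Scaling the signal to a post-test maximal contraction gives it a common reference; it does not make the two tasks equal.

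**Do the tests stand in for the training bouts?**

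Section 3.2 and Table 1 give three sets of six 5-s repetitions in both arms. Taking Table 1's reading of one angle per set, that is 6 × 5 = 30 s of contraction per set and 3 × 30 = 90 s per exercise. The intensity is 100% effort at three angles for ISO-RT and 80% 1RM for DYN-RT. The tests run to failure at 80% MVC at one angle and at 60% 1RM. Neither reproduces the training bout of either arm.

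**Timing of the recording**

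Before-and-after readings and a trace taken during the test yield different quantities. Section 6 uses both descriptions. Neither timing turns a test response into a measure of training demand.

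**The case against.** The strongest case against the point is that no planned analysis is wrong. Section 5.2 already has the time-by-group model. Section 2 frames the aim as the impact of a six-week programme, section 6.1 speaks of adaptations, and the sentence after the disputed one is suitably cautious. On this view all that remains is one loose sentence about a secondary outcome in a pilot that does not set out to test hypotheses. Most of this stands, and it bounds the point. It does not remove it: a sound model followed by an interpretation that it cannot support is still a mismatch, and this sentence is where the article interprets NIRS.

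It is also fair to say that the tests are not unrelated to the training. The dynamic test uses the training cadence and the isometric test uses 5-s contractions. Time to failure is itself an endurance outcome, not simply a mismatched setting. Load, rest, position and stop rule still differ.

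Three stronger readings are tempting, and the document does not support them:

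- **That the trial will report a test-to-test difference as an effect of contraction mode.** No such contrast is planned in section 5.2.
- **That NIRS is never recorded in training sessions.** None is described, but the article is condensed. Its sentence on assessment times is not exhaustive either, since section 4.8 collects soreness after every session. What can be said is that section 6 rests its claim on the endurance tests.
- **That the NIRS outcome is uninformative.** The randomised comparison of change within each test is valid.

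**Conclusion.** The concern holds as a mismatch between a stated conclusion and the planned estimate. As described, NIRS at the endurance tests supports a comparison of how the two programmes change vastus lateralis oxygenation in response to each test. It does not support a direct comparison of the demands that ISO-RT and DYN-RT impose. A dynamic-versus-isometric test comparison would not supply it, because load, duty cycle (80–100% against 50%), position and stop rule change along with contraction mode.

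The size is modest: one secondary outcome, no effect on the primary strength outcomes, and no change to the planned model. The correction should be made because it is nearly free and the pilot's results are meant to shape a larger trial.

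The verdict rests on two assumptions. Both arms take both tests, which is inferred from the Abstract and sections 3.6 and 5.2 and is not stated in one sentence. ISO-RT and DYN-RT in the disputed sentence mean the training programmes, as they do elsewhere in the article.

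**What to change.** 1. In section 6, replace the claim of a direct comparison of demands with the quantity the design estimates: the group-by-time effect on vastus lateralis oxygenation, estimated separately within the dynamic and the isometric endurance test and interpreted as training adaptation.
2. State that differences between the two tests will not be attributed to contraction mode.
3. Reconcile the two descriptions of timing (before and after the tests, or during them) so that the analysed oxygenation measure is defined.

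The first two changes are wording only. The third requires the investigators to state which recording is made. No added recording, visit or participant is needed. The cost is a narrower stated conclusion: the gap named in the Introduction would be addressed as a comparison of training-induced change in oxygenation, not as a comparison of the demands of the two modes.

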### Strengths and potential impact

6.1

This study outlines a rigorously designed pilot trial aimed at comparing the effects of multi-angle ISO-RT and DYN-RT on muscle performance, body composition, and recovery-related responses. While DYN-RT has traditionally been the gold standard for improving muscular strength and hypertrophy, multi-angle ISO-RT offers a promising alternative by potentially overcoming the joint-angle specificity of conventional isometric protocols. Nonetheless, high-quality controlled trials are needed to determine whether these theoretical advantages translate into superior or comparable adaptations in practice.

This trial is among the first to directly compare the muscular adaptations of ISO_RT vs DYN_RT by using two independent groups. The study employs a comprehensive battery of outcome measures, with primary endpoints including dynamic and isometric strength. Secondary outcomes encompass key physiological markers such as muscle hypertrophy, power, muscular endurance, and muscle oxygenation. Collectively, these data will yield preliminary effect estimates and feasibility indicators, informing the design and implementation of future large-scale, adequately powered trials. Ultimately, the findings will contribute to the evidence base needed to guide the development of individualised and context-specific ISO-RT programs.

